| Title                        | Efficacy of Xuebijing Injection in Patient with Sepsis: A Multicentre, Randomized, Blind, Placebo-controlled Trial (EXIT-SEP)                                                                                                                                                                                                                                                                                                                                                                                                                                                                                                                                                                                                                                                                                                                                                                                                                                                                                                                                                                                     |
| Study design                 | A multi-center, randomized, placebo-controlled, double-blind clinical trial of Xuebijing Injection in patients with sepsis.                                                                                                                                                                                                                                                                                                                                                                                                                                                                                                                                                                                                                                                                                                                                                                                                                                                                                                                                                                                       |
| Primary Objective            | To evaluate whether Xuebijing Injection, when administered to subjects with sepsis, can reduce 28-day all-cause mortality.                                                                                                                                                                                                                                                                                                                                                                                                                                                                                                                                                                                                                                                                                                                                                                                                                                                                                                                                                                                        |
| Study Center(s)              | Up to 45 study centers                                                                                                                                                                                                                                                                                                                                                                                                                                                                                                                                                                                                                                                                                                                                                                                                                                                                                                                                                                                                                                                                                            |
| Number of Subjects (planned) | Approximately 1800 randomized subjects                                                                                                                                                                                                                                                                                                                                                                                                                                                                                                                                                                                                                                                                                                                                                                                                                                                                                                                                                                                                                                                                            |
| Subjects                     | 
Inclusion criteria
 
 
1. Subjects is diagnosed with sepsis 3.0
 
2. Age <math>\geq 18</math> and 75
 
3. Subjects had a Sequential Organ Failure Assessment (SOFA) score of 2-13
 
4. Subjects must be receiving treatment in an intensive care unit (ICU)
 
5. Informed consent obtained from patient or acceptable patient surrogate
 
 
Exclusion criteria
 
 
1. Subjects is diagnosed with sepsis for more than 48 hours
 
2. Female who is pregnant or lactating at time of admission
 
3. Had severe primary disease, including unresectable tumours, haematological diseases and human immunodeficiency virus (HIV) infection, had severe liver and kidney dysfunction (was defined as liver or kidney component SOFA score <math>\geq 3</math> points)
 
4. Receiving/used an immunosuppressant, an organ transplant within the previous 6 months
 
5. Participated in other clinical trials in the previous 30 days
 
 |
| Treatments                   | 
Treatment group: Xuebijing injection (100 ml, every 12 hours) diluted in 100 ml 0.9% sodium chloride injection
 
Placebo group: 0.9% sodium chloride injection (200 ml, every 12 hours)
                                                                                                                                                                                                                                                                                                                                                                                                                                                                                                                                                                                                                                                                                                                                                                                                                                                                                                        |
| Duration of Treatment        | Active treatment will continue for 5 days, discharge from study hospital, discharge from the ICU, study withdrawal, or death, whichever comes first.                                                                                                                                                                                                                                                                                                                                                                                                                                                                                                                                                                                                                                                                                                                                                                                                                                                                                                                                                              |
| Follow-up                    | All participants will be followed for a total of 28 days.                                                                                                                                                                                                                                                                                                                                                                                                                                                                                                                                                                                                                                                                                                                                                                                                                                                                                                                                                                                                                                                         |
| Informed Consent             | Explicit written, signed informed consent from the subject or legally authorized representative will be obtained prior to any protocol specific procedures                                                                                                                                                                                                                                                                                                                                                                                                                                                                                                                                                                                                                                                                                                                                                                                                                                                                                                                                                        |
| Randomization                | Subjects will be randomly assigned in a 1:1 fashion to receive Xuebijing Injection or placebo. Randomization occurs immediately after baseline SOFA score via a real-time, internet-based randomization method.                                                                                                                                                                                                                                                                                                                                                                                                                                                                                                                                                                                                                                                                                                                                                                                                                                                                                                   |
| Primary outcome              | 28-day all-cause mortality                                                                                                                                                                                                                                                                                                                                                                                                                                                                                                                                                                                                                                                                                                                                                                                                                                                                                                                                                                                                                                                                                        |
| Secondary outcome            | 
 
1) In ICU mortality
 
2) In hospital mortality
 
3) Length of stay (LOS) in the ICU
 
                                                                                                                                                                                                                                                                                                                                                                                                                                                                                                                                                                                                                                                                                                                                                                                                                                                                                                                                                                      |

|                       |                                                                                                                                                                                                                                                                                                                                                                        |
|-----------------------|------------------------------------------------------------------------------------------------------------------------------------------------------------------------------------------------------------------------------------------------------------------------------------------------------------------------------------------------------------------------|
|                       | 4) LOS in hospital, 28-day cumulative mechanical ventilation-free days
5) 28-day ICU-free days
6) The change in SOFA score on day 3
7) The change in SOFA score on day 6
8) The change in Acute Physiology and Chronic Health Evaluation (APACHE) II score on day 3
9) The change in APACHE II score on day 6 |
| Safety outcome | Incidence of serious adverse events (SAEs)
Incidence of adverse events (AEs)                                                                                                                                                                                                                                                                          |
| Study Timeline | Recruitment period estimated in 36 months
Follow-up per patient: 28 days                                                                                                                                                                                                                                                                              |

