## 4.3 Randomization

This study adopts a third-party interactive web response system (IWRS), which is implemented as competitive enrolment with a randomized block design. The random process is blinded to the investigators. Subjects are assigned to the treatment group and the placebo group at a 1:1 ratio.

When the screened subjects are eligible for recruitment, investigators at subsites log in to the IWRS and enter the subjects' basic information, including their screening numbers and initials, according to the system prompts. The IWRS randomly assigns the subjects SOFA scores (2-7 points vs. 8-13 points) as a stratification factor. The SSID (6 digits) and random number (4 digits) of each subject are unique and bound to each other.

After random numbers are generated, drug managers log in to the IWRS again for the allocation results and then provide this information to study nurses and dispense the investigational products to study nurses for instillation.

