#### 5.2 Secondary outcomes

| Secondary outcomes                                 |                                                                                                                      |
|-----------------------------------------------------------|----------------------------------------------------------------------------------------------------------------------|
| ICU mortality,                                     | The proportion of patients who had died to ICU discharge                                                             |
| Hospital mortality                                 | The proportion of patients who had died to hospital discharge                                                        |
| Length of stay (LOS) in the ICU                    | The total duration of stay in the ICU for the first 28 days after randomization                                      |
| LOS in hospital                                    | The total duration of stay in the hospital for the first 28 days after randomization                                 |
| 28-day cumulative mechanical ventilation-free days | The total number of days a patient was alive and not on mechanical ventilation support from randomization to 28 days |
| 28-day ICU-free days                               | The number of days alive and free of ICU from randomization to 28 days                                               |
| The change in SOFA score on day 3                  | The change in SOFA score from baseline score measured at randomization to the score at Day 3                         |
| The change in SOFA score on day 6                  | The change in SOFA score from baseline score measured at randomization to the score at Day 6                         |

|                                                                                                |                                                                                                   |
|------------------------------------------------------------------------------------------------|---------------------------------------------------------------------------------------------------|
| The change in Acute Physiology and Chronic Health Evaluation (APACHE) II score on day 3 | The change in APACHE II score from baseline score measured at randomization to the score at Day 3 |

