## **8. STATISTICAL CONSIDERATIONS**

### **8.1 Power Calculation and Sample Size**

Based on the previous observational CHESS study conducted in China, a 28-day all-cause mortality rate of 24.3% in the placebo group was assumed in this trial. With a dropout rate of approximately 15%, a sample size of 1800 patients provided 80% power at the two-sided 0.05 significance level on an assumption of an absolute risk reduction of 6% in mortality.

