### **8.2 Analysis of Results**

A senior statistician at Dongzhimen Hospital will perform data analysis on an intention-to-treat basis. Summary statistics will be used to describe the clinical data and presented as mean  $\pm$  SD, or percentages as appropriate. Continuous variables will be compared using a two-sample t-test or Wilcoxon rank-sum test if data show serious deviations from a normal distribution. Categorical data or ordinal data will be compared using a Wilcoxon rank-sum test, chi-square test or Fisher's exact test, as appropriate. All tests will be two-sided. Statistical significance declared for probability values of 0.05 or less. Analysis of the outcome of excluded patients due to other trials etc. will be in accordance with the CONSORT guidelines.

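### Ventilator-free days are compared without regard to ventilation at randomisation: a valid test that gives up precision on a secondary outcome

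*Protocol*

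**What the plan says.** - **Outcome.** The synopsis lists "28-day cumulative mechanical ventilation-free days" among the secondary outcomes. Section 5.2 defines it as "The total number of days a patient was alive and not on mechanical ventilation support from randomization to 28 days". All randomised patients count, whatever their ventilation status at entry.
- **Population.** Sections 3.3 and 3.4 ask for sepsis, ICU care and a SOFA score of 2-13. Ventilation is neither required nor excluded.
- **Randomisation.** Section 4.3 names "SOFA scores (2-7 points vs. 8-13 points) as a stratification factor" and no other factor.
- **Analysis.** Section 8.2 states: "Continuous variables will be compared using a two-sample t-test or Wilcoxon rank-sum test if data show serious deviations from a normal distribution". It names no covariate or stratum for these comparisons, not even the SOFA band used at randomisation.
- **Size.** Section 8.1 sizes the trial on mortality alone. The protocol gives no target difference, standard deviation or power for ventilator-free days, and no expected share of patients ventilated at entry.

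**The concern.** The outcome means different things in two kinds of patient. In someone ventilated at randomisation it reflects weaning and survival, and days are lost from the start. In someone not ventilated it reflects avoiding intubation and survival, and most survivors will sit at or near 28. The difference between these two groups is known before the first infusion and has nothing to do with treatment. In a pooled two-sample test it is still counted as noise.

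At stake is sensitivity: a real effect on weaning or intubation could be missed, or estimated with a wider interval than necessary. The information that would remove the noise is already needed to count ventilated days from randomisation, and section 7.1 has therapeutic interventions collected.

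**Working it through.** **1. The plan's own figure.** Inputs from section 8.1: control mortality 24.3%, reduction 6 points (so 18.3%), two-sided 0.05, 80% power, 15% dropout. With continuity correction, 763 per arm gives 1526 in total, and 1526/0.85 = 1796. Without it, 730 per arm gives 1460, and 1460/0.85 = 1718. The stated 1800 reproduces, but for mortality only. It says nothing about power for ventilator-free days.

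**2. General relation.** If entry ventilation explains a share R² of the outcome variance, then

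unadjusted noncentrality = adjusted noncentrality × √(1 − R²).

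For an adjusted power of 80% the noncentrality is 1.960 + 0.842 = 2.802. At R² = 0.20, 2.802 × √0.80 = 2.506; 2.506 − 1.960 = 0.546, which is a power of 70.7%.

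| R² | Power without adjustment, when adjusted power is 80% |
|---|---|
| 0.05 | 78.0% |
| 0.10 | 75.7% |
| 0.20 | 70.7% |
| 0.30 | 65.0% |
| 0.40 | 58.3% |

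The documents do not give R², so it has to be simulated under stated assumptions.

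**3. Day scale (t-test against adjusted comparison), 900 per arm.** Assumed: 30-70% ventilated at entry, 15% of the others ventilated later, mean ventilation 7 or 10 days, death risk 1.5 or 2.5 times higher if ventilated, overall control mortality 24.3%, and treatment acting only through the planned mortality reduction. R² was 0.07-0.24. The smallest gain was 80.6% to 83.3% (2.7 points) and the largest 49.6% to 61.1% (11.5 points). The smallest arises when deaths are scored as zero days. Scored as section 5.2 defines the outcome, the gains run from 4.6 to 11.5 points. Under the model in step 4, which also shortens ventilation, the t-test at 50% ventilated rises from 44% to 57% and from 73% to 86% for the two effect sizes. Across ventilated shares that model gives about 7-14 points.

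**4. Rank scale (pooled Wilcoxon against van Elteren by entry ventilation), 1800 patients.** Assumed: control mortality 33.5% if ventilated and 15% if not (0.5 × 33.5 + 0.5 × 15 = 24.25, matching the planned 24.3% at a 50% share); 15% intubated later; lognormal ventilation time with median 7 days and log-SD 0.9. The smaller effect is an odds ratio for death of exp(−0.2) with ventilation 10% shorter. The larger is exp(−0.3) with ventilation 14% shorter. At 50% ventilated these are true gains of about 0.9 and 1.4 days.

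| Ventilated at entry | Smaller effect: pooled → stratified | Larger effect: pooled → stratified |
|---|---|---|
| 30% | 22% → 40% | 40% → 70% |
| 50% | 29% → 54% | 56% → 85% |
| 70% | 46% → 63% | 77% → 93% |

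The gains are 16-30 points. Repeat runs fell within about 4 points of these figures. Entry status explained 36-45% of the rank variance, and stratifying cut the variance of the mean difference by 20-28%.

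**5. How far the assumed mortality gap matters.** If mortality is the same whether or not the patient is ventilated at entry, and the effect on death is near the planned one, the Wilcoxon gain falls to about 8-16 points (for example 47% to 59% at 50% ventilated).

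**6. Validity.** With no treatment effect, rejection rates were close to 5% for pooled and stratified tests alike. None of these simulations used the SOFA stratification.

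**The case against.** The strongest case against is that nothing here is wrong. The stated test is valid, the outcome is one of about ten secondary outcomes, and covariate adjustment is often settled in a statistical analysis plan, which is not to hand. That limits the weight of the point but does not remove it: section 8.2 is not silent. It commits to particular unadjusted tests, and a better one is available at almost no cost.

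Several stronger readings are tempting and are not supported:

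- *Entry ventilation is the strongest predictor, or dominates the variance.* The documents say nothing about its prognostic strength. Even under the favourable model it explains less than half of the rank variance (36-45%), and less on the day scale.
- *Much of the power is lost.* That depends on the test and the assumptions. Section 8.2 names the t-test first, and there the gain is modest. The large figures belong to the Wilcoxon test with a wide mortality gap. On the other side, a score bounded at 0 and 28 with clumps at both ends would probably trigger the switch to Wilcoxon, so the rank scale cannot be set aside.
- *Chance imbalance biases the result.* At 50% ventilated, the difference between arms in ventilated share has SD √(0.25 × 4/1800) = 2.36 percentage points. With an entry-status gap of about 11 days in the model, that moves the crude contrast by 0.0236 × 11 = 0.26 days per SD. This is ordinary sampling error, already in the unadjusted standard error. It is the same loss seen from another side, not a second harm.

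It is also fair to say that SOFA stratification may balance ventilation in part. The documents do not allow that to be quantified.

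**Conclusion.** The point holds as a loss of efficiency on a secondary outcome. The protocol pools patients ventilated and not ventilated at randomisation, balances on SOFA only, and names unadjusted tests, so variance predictable from entry status is left in the error. With 1800 patients and 30-70% ventilated, the recoverable power is roughly 3-14 points on the day scale and roughly 8-30 points on the rank scale. Of the inputs that drive these ranges, the documents supply only the sample size, the 24.3% control mortality and the 6-point reduction. The ventilated share, mortality by entry status, later intubation and ventilation times are assumptions, and the assumed effects on ventilation are too. The type I error is sound, the estimate is not biased, and the conclusion on 28-day mortality is untouched.

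**What to change.** In section 8.2, add that ventilator-free days will be compared with a van Elteren test stratified by mechanical ventilation at randomisation (yes or no) and by the SOFA randomisation stratum (2-7 or 8-13). Where the t-test would have been used, use instead a linear model adjusted for both factors. Report the stratum-weighted mean difference with its 95% CI.

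Define ventilation status as recorded at randomisation, before the first study infusion. A calendar-day record will not do for this, because day 0 in section 7.1 runs to the end of the day of randomisation and could include ventilation begun after treatment started.

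The cost is a sentence or two of analysis text and one derived variable, with no extra patients or procedures. The only trade-off is that the reported difference is stratum-weighted instead of crude.
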